### Sample size calculation

Power calculations were conducted to determine the sample size required to detect changes in mental health related outcomes resulting from martial arts training. Statistical power calculations assumed baseline-post-test expected effect size gains of *d* = 0.3, and were based on 90% power with alpha levels set at *p* < 0.05. The minimum completion sample size was calculated as *n* = 234 (intervention group: *n* = 117, control group: *n* = 117). As participant drop-out rates of 20% are common in randomised controlled trials [14], the maximum proposed sample size was *n* = 293 (intervention group: *n* = 147, control group: *n* = 146).

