### Statistical methods

Statistical analysis of the primary and secondary outcomes will be conducted using SPSS statistics version 25 (IBM SPSS Statistics, 2017) and alpha levels will be set at *p* < 0.05.

The collected psychometric test data will be consolidated into subscale variables using factor analysis and the internal consistency of each variable will be examined to determine reliability. Items to be included in the scale variables will be added and computed to create composite scores. Repeated measures univariate analysis of variance (ANOVA), and multivariate analysis of variance (MANOVA) will primarily be used to analyse test data. Ordinal regression will be used to analyse test data based on psychometric measures using a 3-point Likert scale. Interpretation of effect sizes will reflect Cohen’s suggested small, medium, and large effect sizes, where partial eta squared sizes are equal to 0.10, 0.25, and 0.40 respectively [25].

Age, school grade level, sex, socio-economic status and cultural background will be included as covariates in the analysis.

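### The benchmarks 0.10, 0.25 and 0.40 are labelled partial eta squared but are Cohen's f values; applied literally, they would grade ANOVA and MANOVA effects too low.

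*Protocol article*

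**What the plan says.** The Statistical methods section names the main analyses: "Repeated measures univariate analysis of variance (ANOVA), and multivariate analysis of variance (MANOVA) will primarily be used to analyse test data". It then says that magnitude will be described by Cohen's three grades and ties those grades to numbers: "where partial eta squared sizes are equal to 0.10, 0.25, and 0.40 respectively". Both the scale and the three cut-offs are therefore fixed in the text. Cohen's f is not mentioned anywhere in the article, and no other section qualifies the cut-offs.

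The Sample size calculation section works on a different scale. The power calculation "assumed baseline-post-test expected effect size gains of *d* = 0.3", with 90% power, an alpha of 0.05 and 117 completers per arm.

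**The concern.** Cohen's f and partial eta squared are linked by algebra but are different quantities. At the sizes at issue, partial eta squared is much the smaller of the two. Putting f benchmarks on the partial eta squared scale raises the bar for every grade.

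The article states no other rule for turning an ANOVA or MANOVA effect into words. If it is followed as printed, a result equal to the planned effect would be reported as less than small. The trial's size descriptions would then not be comparable with the small and medium effects that the Background section reports from the earlier meta-analysis. The article also presents the findings as relevant to public health and school policy, where such words carry weight.

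**Working it through.** **Inputs.** Cut-offs 0.10, 0.25 and 0.40, labelled partial eta squared (Statistical methods). Planned effect d = 0.3, 117 completers per arm, 234 in total, 90% power, alpha 0.05 (Sample size calculation; two-sided testing is assumed, as sidedness is not stated). The pre-post correlation r is not given, so a range is shown as an assumption. The conversions below are for a single outcome without covariates.

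**Step 1: which scale reproduces the printed numbers.** For two equal groups f = d/2, and partial eta squared = f²/(1 + f²).

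| Conventional grade | d | f = d/2 | Partial eta squared | Printed cut-off | Printed / matching |
|---|---|---|---|---|---|
| Small | 0.2 | 0.10 | 0.01/1.01 = 0.0099 | 0.10 | about 10 |
| Medium | 0.5 | 0.25 | 0.0625/1.0625 = 0.0588 | 0.25 | about 4 |
| Large | 0.8 | 0.40 | 0.16/1.16 = 0.1379 | 0.40 | about 3 |

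The printed numbers match the f column exactly and do not match the partial eta squared column.

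**Step 2: what the printed cut-offs mean if taken literally.** The inverse is f = √(η²/(1 − η²)). Values of 0.10, 0.25 and 0.40 give f = 0.333, 0.577 and 0.816. For a plain two-group comparison these are d = 0.67, 1.15 and 1.63.

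**Step 3: where the planned d = 0.3 falls.**

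- *Two-group comparison:* f = 0.15, so η² = 0.0225/1.0225 = 0.022.
- *Group-by-time interaction, two time points:* f = (0.3/2)/√(2(1 − r)). Two time points apply because, under Study design, the control group is not measured at follow-up.

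| Assumed r | Partial eta squared |
|---|---|
| 0 | 0.011 |
| 0.5 | 0.022 |
| 0.7 | 0.036 |
| 0.75 | 0.043 |
| 0.8 | 0.053 |
| 0.85 | 0.070 |
| 0.9 | 0.101 |

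- *Paired (within-arm) reading:* f = d = 0.3, so η² = 0.09/1.09 = 0.083.

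Two of these readings also reproduce the stated 117 per arm, each giving 116.7: a paired calculation, and change scores with r = 0.75. Their values, 0.083 and 0.043, are both below 0.10.

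**Step 4: significance against grade.** With N = 234, a one-degree-of-freedom between-group effect reaches p = 0.05 at a partial eta squared of about 0.016. Significant effects between about 0.016 and 0.10 would be described as less than small.

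**The case against.** The best defence is that only the label is wrong. Because the numbers are exactly the f values, the authors may have meant f; an analyst who computes and grades f would grade correctly. That is plausible, and it is why the consequence is conditional on literal use. It does not make the sentence right, since the named scale is partial eta squared.

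A second objection is that the rule sets only an adjective. Significance is judged separately at 0.05, and grade is not a success criterion. Any reader given partial eta squared can re-grade it. This stands and limits the seriousness of the error.

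Third, the d conversions depend on the model, and this also stands. A reader might infer that even a conventional large effect, d = 0.8, would be called small. That holds for a two-group comparison (0.138) or an interaction with r = 0.5, but not generally. With r = 0.8, f² = 0.16/0.4 = 0.40 and partial eta squared is 0.40/1.40 = 0.286, which the printed rule calls medium. The paired reading gives 0.64/1.64 = 0.39, also medium. Likewise, the printed threshold for small is d = 0.67 for two groups, about 0.47 for an interaction with r = 0.75, and 0.33 on the paired reading.

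Finally, a reader might infer that every result is affected. The same section assigns ordinal regression to measures on a 3-point scale; that method does not yield partial eta squared, so the rule does not reach those results.

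**Conclusion.** The printed cut-offs are wrong for the scale they name, by factors of about 10, 4 and 3. This follows from algebra and does not depend on the pre-post correlation.

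The conflict with the planned effect depends on the model, but its direction is stable. Applied literally, the rule grades d = 0.3 below small on the two-group and paired readings, and on the interaction reading for any pre-post correlation below about 0.9. The shortfall ranges from slight (0.083 against 0.10, paired) to about one ninth of the cut-off (0.011, interaction with r = 0).

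The documents do not support a claim that the trial's inference is compromised: the error leaves tests, p-values, type I error and power as they are. Nor do they show that misgrading is certain, since an analyst working in f would grade correctly.

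**What to change.** Replace the cut-offs with partial eta squared 0.01, 0.06 and 0.14 (Cohen's f 0.10, 0.25 and 0.40). Alternatively, keep the printed numbers, label them Cohen's f and report f. Either one cures the error.

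The cost is one sentence, with no change to design, data collection or tests. It should be made before effect sizes are interpreted.

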## Discussion

The primary aim of this study is to evaluate the training effects of martial arts participation on mental health outcomes. The study will use a randomised controlled trial of secondary school aged participants.

Previous studies examining the impact of martial arts training on mental health and wellbeing have found positive results, which has also been confirmed by a systematic review and meta-analysis. Results have included martial arts training reducing symptoms associated with anxiety and depression; and promoting characteristics associated with wellbeing. However, the small number of relevant studies and noted methodological problems lead to uncertainty regarding the validity and reliability of existing research.

The current study utilises a robust design with baseline, post-test and follow-up measures to examine the views of participants and includes a rigorous evaluation process using quantitative data to explore the program’s potential efficacy. This is a clear strength of this study and is important due to the study’s multi-site delivery. The current study has not used a qualitative approach which is a limitation of the research. Qualitative work is planned for future research to explore issues such as mechanism of impact.

### Conclusion

The findings of this study will provide valuable evidence regarding the training effects of martial arts participation on mental health outcomes, and information for research groups looking for alternative or complementary psychological interventions. To our knowledge, no previous studies have reported the training effects of martial arts participation on mental health outcomes on a scale comparable to the current study while maintaining a similarly robust design and rigorous evaluation process. This study has the potential to change public health policy, and school-based policy and practice regarding management of mental health outcomes and enhance a range of health promoting behaviours in schools.

## Data Availability

The datasets used and/or analysed during the current study will be available from the corresponding author on reasonable request.

## Abbreviations

$AUD: Australian dollar
$USD: United States dollar
ACTRN: Australian New Zealand Clinical Trials Registry Number
ANOVA: Analysis of variance
CONSORT: Consolidation standards of reporting trials
CYRM: Child and youth resilience measure
MANOVA: Multivariate analysis of variance
NSW: New South Wales
SDQ: Strengths and difficulties questionnaire
SEQ-C: Self-efficacy questionnaire for children
SPSS: Statistical packages for the social sciences
